## Abstract

**Introduction:**

For people with type 2 diabetes mellitus (T2DM) who require an antidiabetic drug as an add-on to metformin, there is controversy about whether newer drug classes such as dipeptidyl peptidase-4 inhibitors (DPP4i) or sodium-glucose co-transporter-2 inhibitors (SGLT2i) reduce the risk of long-term complications compared with sulfonylureas (SU). There is widespread variation across National Health Service Clinical Commissioning Groups (CCGs) in drug choice for second-line treatment in part because National Institute for Health and Care Excellence guidelines do not specify a single preferred drug class, either overall or within specific patient subgroups. This study will evaluate the relative effectiveness of the three most common second-line treatments in the UK (SU, DPP4i and SGLT2i as add-ons to metformin) and help target treatments according to individual risk profiles.

**Methods and analysis:**

The study includes people with T2DM prescribed one of the second-line treatments-of-interest between 2014 and 2020 within the UK Clinical Practice Research Datalink linked with Hospital Episode Statistics and Office of National Statistics. We will use an instrumental variable (IV) method to estimate short-term and long-term relative effectiveness of second-line treatments according to individuals’ risk profiles. This method minimises bias from unmeasured confounders by exploiting the natural variation in second-line prescribing across CCGs as an IV for the choice of prescribed treatment. The primary outcome to assess short-term effectiveness will be change in haemoglobin A1c (%) 12 months after treatment initiation. Outcome measures to assess longer-term effectiveness (maximum ~6 years) will include microvascular and macrovascular complications, all-cause mortality and hospital admissions during follow-up.

**Ethics and dissemination:**

This study was approved by the Independent Scientific Advisory Committee (20-064) and the London School of Hygiene & Tropical Medicine Research Ethics Committee (21395). Results, codelists and other analysis code will be made available to patients, clinicians, policy-makers and researchers.

Strengths and limitations of this studyThis large representative study of UK clinical practice will describe variation in second-line antidiabetic treatment for people with type 2 diabetes mellitus.The instrumental variable (IV) design will minimise bias due to confounding by indication and provide person-level estimates of second-line treatment effectiveness.The IV design relies on assumptions which can only be partly tested using the data available.We will not consider less commonly used injectable second-line antidiabetic treatments in the UK, namely glucagon-like peptide-1 receptor agonists and insulin.

## Introduction

Around 3.5 million people in the UK have been diagnosed with type 2 diabetes mellitus (T2DM) accounting for ~10% of National Health Service (NHS) expenditure.^1^ This proportion is predicted to rise to ~17% by 2035–2036.^2^ T2DM is a progressive disease which requires careful management of blood glucose and diabetes-associated complications.^1^ The National Institute for Health and Care Excellence (NICE) recommends metformin as the first-line antidiabetic treatment in people with T2DM.^1^ In many cases, people with T2DM need further treatment in addition to metformin monotherapy to maintain sufficient glycaemic control.

NICE guidance recommends several drug classes as add-ons to metformin for first-stage intensification, hereafter referred to as second-line treatment. These include sulfonylureas (SU), pioglitazone, dipeptidyl peptidase-4 inhibitors (DPP4i) or sodium-glucose co-transporter-2 inhibitors (SGLT2i).^1 3^ NICE guidance recommends considering individual clinical circumstances when selecting T2DM drug treatment. For instance, SGLT2i are recommended as second-line treatment if the person is at high risk of hypoglycaemia or when SU are not tolerated or are contraindicated.^1 3^ However, these guidelines do not specify a single preferred drug class, either overall or within specific groups sharing clinical characteristics.^1^ Research using a representative sample of the UK primary care population up to 2017 showed that SU, DPP4i and SGLT2i, each in combination with metformin, are the most commonly prescribed second-line treatments.^4^

There is wide variation in the proportion of people prescribed these drugs in addition to metformin across NHS Clinical Commissioning Groups (CCGs), who commission local NHS services, suggesting clinician preference may influence treatment choice.^4^ In particular, the variation in SGLT2i prescribing suggests that some clinicians may prescribe these drugs even for those patients who are not considered at high risk of hypoglycaemia and therefore eligible for SU.

Similar to NICE guidance, an international consensus statement published in 2018 did not specify a single preferred drug class for second-line treatment, but recommended that choice is ‘personalised’ to individual characteristics and risk profiles. This statement was updated in 2019 in light of new evidence supporting SGLT2i or glucagon-like peptide-1 receptor agonist (GLP1RA) use after metformin for those with atherosclerotic cardiovascular disease (CVD), or those at high CVD risk.^5^ However, regulators, clinicians and patients remain uncertain about how best to tailor second-line antidiabetic treatment based on individual characteristics.

Meta-analyses have reported that compared with other antidiabetic treatments, second-generation or third-generation SU are not associated with higher risk of death or cardiovascular (CV) events.^6 7^ A recent CV outcome trial reported that the safety profile of glimepiride (SU drug class) was similar to linagliptin (DPP4i drug class).^8^ Several placebo-controlled trials reported that SGLT2i reduced major CV events in people with T2DM.^9–12^ While head-to-head randomised controlled trials (RCTs) can provide unbiased estimates of relative effectiveness, the range and number of participants included in head-to-head RCTs of alternative second-line treatments are insufficient to provide reliable estimates of long-term effectiveness according to individual-level risk profiles.^13–15^

Observational studies comparing outcomes of alternative second-line drug regimens have reported that SU, DPP4i and SGLT2i combined with metformin are all associated with haemoglobin A1c (HbA1c) reductions compared with metformin alone^16 17^; however, some reported that SU are associated with higher risk of CV events.^7 18^ These observational studies did not recognise that people who receive SU may have been a more severe case mix according to unmeasured prognostic variables (eg, frailty) meaning results are likely biased due to confounding by indication.^19^

### Aims and objectives

This study aims to investigate the relative effectiveness of SU, DPP4i or SGLT2i in combination with metformin as second-line antidiabetic drug treatments on key T2DM outcomes, and how treatment decisions should be tailored to an individual’s risk factor profile to maximise clinical benefit. We will use advanced quantitative methods to minimise the impact of confounding by indication and allow for heterogeneity according to patient characteristics.

The study’s objectives are to: (1) Describe baseline characteristics and treatment patterns overall, and by clinically important subgroups, for SU, DPP4i and SGLT2i in combination with metformin as second-line T2DM treatment; (2) Estimate the relative short-term (12 month) effectiveness of SU, DPP4i or SGLT2i combined with metformin on levels of HbA1c, overall and according to individual risk-factor profiles and (3) Estimate the long-term (maximum ~6 years) effectiveness of SU, DPP4i or SGLT2i combined with metformin on incident microvascular and macro-vascular complications, overall and according to individual risk-factor profiles.

## Methods and analysis

### Data resources

We will identify the study population using the UK Clinical Practice Research Datalink (CPRD),^20 21^ a pseudonymised primary care database which includes detailed demographic/lifestyle data, clinical diagnoses and measurements, primary care prescriptions, referrals and laboratory test results for approximately 20% of the UK population. Both the CPRD Gold and Aurum datasets will be used to identify people eligible for inclusion, providing a representative population of people with T2DM eligible for the second-line treatments of interest.^20 21^

Linkage to Hospital Episode Statistics (HES) is available for approximately 70% of English practices and will be used to gather secondary care data for the study population. HES Admitted Patient Care data includes complete in-patient admissions data to all NHS hospitals in England.^22^ These secondary care data include admission and discharge dates, diagnoses and other descriptive information (eg, ethnicity). Linkages will also be made to the Office of National Statistics to obtain mortality data and the Index of Multiple Deprivation (IMD) as a person-level proxy of socioeconomic status (SES).

### Sample selection/study population

The study population will include people registered with a CPRD-contributing practice, aged 18 years or older, diagnosed with T2DM who intensify antidiabetic treatment from metformin-monotherapy to a combination of metformin and SU, DPP4i or SGLT2i (second-line treatment) between 2014 and 2020 (figure 1).

**Figure 1 F1:**
[figure not shown]
Flow diagram illustrating the identification of the study cohort of people with type 2 diabetes mellitus (T2DM) who initiate second-line antidiabetic treatment with metformin and one of sulfonylurea (SU), dipeptidyl peptidase four inhibitor (DPP4i) or sodium-glucose cotransporter two inhibitors (SGLT2i). CPRD, Clinical Practice Research Datalink; eGFR, estimated glomerular filtration rate; HES, Hospital Episode Statistics; MTF; metformin.

We will identify people within CPRD with at least one prescription for metformin monotherapy and one other antidiabetic medication in primary care between 1 January 2011 and 31 March 2020, registered at a general practice (GP) contributing research-quality data at the prescription date, and registered with their GP for at least 1 year prior to the first metformin or other antidiabetic prescription, to ensure that we are studying new users. The study population will be limited to people with a T2DM primary care code, on or before the antidiabetic index date to exclude those prescribed antidiabetic medications for other indications (eg, polycystic ovarian syndrome or pre-diabetes). Using the individual’s entire prescribing history with their registered GP, we will include only people who initiate antidiabetic treatment with metformin, and intensify metformin-monotherapy with a first-time prescription for one of the three second-line antidiabetic drug treatments of interest after 1 January 2014. We chose this date for the evaluation of these three treatments as prior to this only a small minority of people in the UK were prescribed SGLT2i.^4^ People who intensify with two or more drug classes on the same date, who discontinue metformin monotherapy prior to a prescription for SU, DPP4i or SGLT2i, or who are prescribed a different drug class as second-line treatment (eg, thiazolidinedione (TZD), insulin, GLP1RA) will be excluded. In addition, we will exclude people with estimated glomerular filtration rate (eGFR) below 30 mL/min/1.73m^2^ since SGLT2i are contraindicated for this group.^23^ We will also exclude women who were pregnant in the 12 months prior to second-line treatment initiation since prescribing guidelines recommend different treatments for pregnant and breastfeeding women.^24^

### Exposures

Exposure groups will include people prescribed SU, DPP4i or SGLT2i as an add-on to metformin. We will not consider other less commonly prescribed T2DM intensification treatments namely TZD, insulin and GLP1-RA since these treatments combined account for less than 10% of second-line therapy regimens in the UK.^4^

The first prescription date for second-line treatment will be considered baseline. To reduce misclassification of people who switch treatments rather than add-on to metformin, we require an additional prescription for metformin on the same date or within 60 days after the first prescription for the second-line drug prescription (SU, DPP4i or SGLT2i). This follows precedent research which used the same definition for second-line antidiabetic treatment in the same database.^4 25^ The study will take an intention-to-treat approach, where each person will contribute to the original exposure group to which they were assigned, irrespective of which treatments they may be prescribed subsequently. People will remain exposed until the date the data are censored by death, the patient leaving the GP practice, the GP practice stops contributing to CPRD, or 31 July 2020. We will use the prescription duration recorded in primary care, plus a 60-day grace-period to account for stock-piling medicines, to mark the end of a prescription. Where these data are missing, we will impute the length of prescription with the mean duration of prescription at the practice level, plus the 60-day grace-period, to mark the end of a prescription. Data on subsequent anti-diabetic treatments (third line, fourth line, etc) will be described in those who discontinue second-line treatment.

The study requires information on each person’s adherence to antidiabetic treatments. First, to provide a ‘baseline’ measure of adherence, we require a measure of each person’s adherence to metformin monotherapy in the year prior to second-line treatment. We will then assess whether baseline adherence modifies the relative effectiveness of the alternative second-line treatments. Second, we will calculate treatment adherence during the follow-up to help interpret the estimates of the relative effectiveness of the alternative second-line treatments. For both measures of adherence, we will calculate defined daily dose (DDD) from the number of tablets and dosage instructions prescribed versus the duration of the period in question.

### Covariates

We will use primary care demographic data, diagnosis codes (Read or SNOMED for CPRD Gold and Aurum, respectively), and laboratory test results recorded prior to second-line treatment initiation, to define our main list of potential confounders. These include age, sex, IMD, time on first-line antidiabetic treatment (as a proxy for diabetes duration), GP size, relevant coprescriptions prescribed within 60 days of second-line treatment initiation (renin-angiotensin system inhibitors, statins), history of proteinuria and comorbidities at baseline (myocardial infarction (MI), unstable angina, stroke, ischaemic heart disease, hypoglycaemia, congestive heart failure (CHF), chronic kidney disease (CKD), end-stage renal disease (ESRD), cancer (any), advanced eye disease and lower extremity amputation). CKD status will be defined using serum creatinine test results to derive eGFR, using cut-points defined by the Kidney Disease Improving Global Outcomes guidelines for CKD, but without requiring two measures 3 months apart.^26^ We will also identify HbA1c, systolic blood pressure (SBP), diastolic blood pressure (DBP), eGFR, body weight and body mass index (BMI)^27^ using values recorded in the 180 days period before the second-line antidiabetic treatment initiation date in the primary care record. Time between baseline clinical measures and second-line treatment initiation will also be included as covariates. We will follow previous observational research,^28^ in undertaking secondary analyses that include additional potential confounders that are defined in primary care records, but for which we anticipate relatively high levels of missing data, namely: ethnicity, high-density lipoprotein (HDL), low-density lipoprotein (LDL), total cholesterol, triglycerides, smoking and alcohol status. In the HES-linked cohort, we will use International Classification of Diseases 10th Revision (ICD-10) diagnosis codes recorded as part of previous hospitalisations in conjunction with primary care data to define comorbidities. We will also use ethnicity recorded in HES for people whose ethnicity is missing within the primary care data. Codelists for all covariates defined in primary and secondary care will be published alongside study results.

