### Planned analyses

We will examine the relevant trends in prescribing between 2014 and 2020 by CCG, and by year, and summarise baseline covariates using data collected prior to the index date for second-line treatment.

We will provide personalised estimates of treatment effectiveness using the local IV (LIV) approach^33 37^ to predict the counterfactual outcomes that each person would experience if they were prescribed each second-line treatment. We will use probit regression models^38^ to estimate the propensity to receive each treatment according to observed characteristics, and CCG preference for each second-line regimen (the IV). We will estimate the relationship of each outcome with observed characteristics, and the propensity for each second-line treatment using generalised linear models (GLMs)^39^ for continuous and count outcomes. For time-to-event outcomes (eg, time to second-line treatment cessation, time to each microvascular or macrovascular complication), we will recognise that the period of observation may differ across individuals due to censoring. We will describe each endpoint by plotting Kaplan-Meier curves, and estimate each treatment effect using discrete-time hazard models.^40^ SEs will be calculated with non-parametric bootstrapping, and will account for clustering of individuals within practices.

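### Diabetes duration enters the models only as time on metformin; the dated T2DM code required at entry would let recorded duration be added at almost no cost

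*Protocol article*

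**What the plan says.** The Covariates section puts "time on first-line antidiabetic treatment (as a proxy for diabetes duration" in the main list of potential confounders. Under Sample selection/study population, "we will include only people who initiate antidiabetic treatment with metformin", so for this cohort the first-line clock starts at the first metformin prescription.

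The same section states the entry rule: "The study population will be limited to people with a T2DM primary care code, on or before the antidiabetic index date". It also requires people to be "registered with their GP for at least 1 year prior to the first metformin or other antidiabetic prescription".

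The Covariates section already names "diagnosis codes (Read or SNOMED for CPRD Gold and Aurum, respectively), and laboratory test results recorded prior to second-line treatment initiation" as sources for the confounders. Time since diagnosis is in neither the main list nor the list of additional confounders for secondary analyses. It is not among the named subgroups in Planned analyses, and Sensitivity analyses names no alternative definition of duration. No reason is given for using the proxy.

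Under Planned analyses, probit models "estimate the propensity to receive each treatment according to observed characteristics, and CCG preference for each second-line regimen (the IV". The outcome models use the same observed characteristics together with the propensity, and person-level effects are differences between the resulting predictions.

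**The concern.** The Introduction describes the condition in these terms: "T2DM is a progressive disease which requires careful management of blood glucose and diabetes-associated complications". The study's purpose is to tailor second-line choice to individual risk profiles, so how long a person has had the disease is a natural part of the profile.

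Time on metformin does not separate two different histories. One person was diagnosed 8 years ago, managed without drugs for 7 years and has taken metformin for 1. Another was diagnosed and started metformin 1 year ago. Both have the value 1 year on this covariate. The first is late escalation in long-standing disease and the second is rapid metformin failure in new disease.

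Three things are at stake:

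- **Precision.** Any prognostic effect of pre-metformin time that the other covariates do not capture stays in the residual.
- **The IV balance check.** The IV assumptions section supports its second assumption by showing balance on observed covariates, and concedes that unmeasured ones cannot be tested. Leaving recorded duration off the list puts a checkable variable among the uncheckable ones.
- **Person-level effects.** They cannot be conditioned on, or reported by, a variable that is not in the models.

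**Working it through.** The plan gives no figure on this point, so there is nothing to reproduce. The check is a reading of the sections against one another, followed by an illustration on assumed inputs.

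**Reading**

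1. Let T be time from first metformin to second-line initiation, G the time from first T2DM code to first metformin, and D = T + G the recorded duration. The covariate list contains T. It contains neither D nor G.
2. The cohort is "limited to people with a T2DM primary care code, on or before the antidiabetic index date". Applying that rule means reading the date of a code, so D can be computed for every eligible person and adds no loss to the complete-case analysis set out under Missing data.
3. The article does not say whether the antidiabetic index date is the first metformin or the second-line prescription. If it is the metformin date, G is zero or positive. If it is the second-line date, some first codes could fall after metformin started and G could be negative. D is computable either way.
4. Because D = T + G, entering D and T together is equivalent in a linear predictor to entering T and G. The models gain one term.

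**How much of D does T miss?**

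The share of Var(D) not explained by T is Var(G)(1 − r²)/Var(D), with r the correlation of T and G and Var(D) = Var(T) + Var(G) + 2r·SD(T)·SD(G). All inputs are assumptions. With SD(T) = 3 years and r = 0:

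| SD(G), years | Calculation | Share missed |
|---|---|---|
| 0.5 | 0.25 / (9 + 0.25) | 3% |
| 1 | 1 / (9 + 1) | 10% |
| 2 | 4 / (9 + 4) | 31% |
| 4 | 16 / (9 + 16) | 64% |

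With SD(T) from 2 to 4 years and r from −0.3 to 0.3, the range is about 1% to 96%. This measures duration missed before any credit for the other covariates. It is not an effect on a treatment estimate.

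**Does omitting G bias the overall estimate?**

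One simulated data set of 400,000 people was run per scenario, with a simple linear IV estimator rather than the planned local IV. Assumed model: Y = −0.3A + 0.05T + 0.1G + noise, with treatment A depending on the instrument and on G, and G left out of the fit.

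| Scenario | Ordinary regression | IV |
|---|---|---|
| Instrument unrelated to G | −0.25 | −0.30 |
| G shifts 0.1 year per SD of instrument | −0.24 | −0.27 |

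The true effect is −0.30. The IV estimate recovers it when the instrument is independent of G. It moves only when an association is assumed, and nothing in the documents reports one.

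**The case against.** The case for leaving the plan alone is substantial.

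- **Disease stage is recorded elsewhere.** A reader might infer that stage is modelled by metformin time alone. It is not: the main list also has HbA1c, eGFR, CKD, ESRD, proteinuria, advanced eye disease, amputation, several cardiovascular conditions and age. The two people in the example share one covariate value and need not share the others. Only the residual information in pre-metformin time is at issue. This stands.
- **The design does not rest on adjustment alone.** A reader might infer biased treatment effects. The overall IV estimate is unaffected if the instrument is independent of G. The article reports balance on observed covariates in pilot data and undertakes to reassess each assumption in the full dataset. This stands.
- **The local IV estimator allows heterogeneity on unobserved characteristics.** It is therefore too strong to say that person-level effects cannot vary with duration, since they may do so through that route and through correlated covariates. What remains is that they cannot be conditioned on or reported by recorded duration.
- **The first code is not the diagnosis.** Only 1 year of registration before the first antidiabetic prescription is required. For someone with long-standing disease managed without drugs who changed practice, the first code in the record may postdate diagnosis. A reader might infer that an exact, complete duration is available; a dated code is, exact duration is not. This limits the gain but does not defeat the proposal, because the new variable is added beside time on metformin rather than replacing it.
- **The proxy is declared, the list is introduced non-exhaustively, and this is a condensed article.** So this is neither a contradiction nor an omission to be charged to the plan. But the article does state how duration will be represented, and that stated choice is open to comment.

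**Conclusion.** The point holds as a low-cost improvement, not as an error. The plan represents duration by a declared proxy that omits disease time before metformin, although its own entry rule supplies a dated code for everyone. The consequences are some residual variance, an IV balance check without a prognostic variable that could be checked, and person-level effects that cannot be conditioned on or reported by recorded duration.

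The size cannot be determined from the documents. A reader might try to express it as average years missed: if 30% to 50% of people had a pre-metformin interval averaging 2 to 4 years, the mean understatement would be 0.30 × 2 = 0.6 to 0.50 × 4 = 2.0 years. Those inputs are assumed. A constant understatement would in any case be absorbed by the model intercept, so only variation in the interval matters. The documents do not support a claim that any HbA1c or complication estimate is biased.

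The conclusion rests on two assumptions: that pre-metformin time has some prognostic value beyond the listed covariates, and that the first-code date carries some information about it.

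**What to change.** In Covariates, add time from first recorded T2DM code to second-line initiation to the main list. Keep time on first-line treatment as a separate covariate, described as such. Use both in the propensity and outcome models. Include recorded duration in the covariate-balance check across levels of CCG prescribing history when the IV assumptions are reassessed on the full dataset.

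State which prescription the antidiabetic index date refers to, so that the sign and meaning of the pre-metformin interval are clear.

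The cost is one derived variable from data already needed for eligibility, one further term in each model, and no loss of complete cases. The limitation to state is that the first-code date may postdate true diagnosis for people who changed practice, so the variable should be described as recorded duration.
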